## Abstract

**Background and aims:**

Acute radiation-induced intestinal injury (ARII) usually occurs after pelvic radiotherapy. Glucocorticoids are potentially effective for the treatment of ARII due to their anti-inflammatory properties, but the currently available evidence is insufficient. Herein, we have designed a multicenter randomized controlled trial (RCT) to explore the efficacy and safety of glucocorticoids for the treatment of ARII.

**Methods:**

Overall, 60 patients with ARII will be enrolled. Eligible patients will be stratified according to the grade of ARII and randomly assigned at a ratio of 1:1 to the routine treatment alone and in combination with local glucocorticoids groups. The primary endpoints include the recovery and improvement of ARII. The secondary endpoints include the recurrence and aggravation of ARII and adverse events of glucocorticoids.

**Discussion:**

This RCT will provide high-quality evidence to clarify the role of local glucocorticoids for the treatment of ARII.

**Clinical trial registration:**

ClinicalTrials.gov, identifier NCT06410443.

## 1 Introduction

Radiotherapy, one of the mainstay treatments for malignant solid tumors in clinical practice, is necessary in nearly half of patients who receive anti-tumor therapy (Citrin, 2017). In spite of constant improvement in radiotherapy-related technology, toxic side effects of radiation on normal tissues are still unavoidable. Considering intestine as a radiation-sensitive organ, radiation-induced intestinal injury (RII) is frequently observed in patients who receive pelvic radiotherapy (Hauer-Jensen et al., 2014). Acute RII (ARII) often refers to significantly progressive abdominal pain, diarrhea, and tenesmus with 3 months since the course of radiotherapy (Hauer-Jensen et al., 2014; Abu-Sbeih et al., 2023; Hovdenak et al., 2000). Serious complications, such as perforation, obstruction, and fistula, may also develop, compromising the patients’ quality of life and outcomes (Gami et al., 2003).

ARII is pathologically characterized as cell death and inflammation response in acute phase. Radiation can damage not only tumor cells by directly or indirectly affecting the synthesis of DNA chains, but also intestinal epithelial cells due to their relatively high mitotic capacity (Spyropoulos et al., 2011). Death of epithelial cells leads to intestinal mucosal breakdown and further induces inflammation. Infiltration of inflammatory cells can be observed in the lamina propria (Hovdenak et al., 2000; Starzewski et al., 2006). Inflammatory process is then amplified by the recruitment and transmigration of monocytes and the activation of resident mast cells, stimulating the production of pro-inflammatory cytokines, such as interleukin (IL) and tumor necrosis factor-α (TNF-α) (Francois et al., 2013).

According to the current practice guidelines, glucocorticoids have been widely recommended for the management of inflammatory bowel disease due to their anti-inflammatory effects (Lamb et al., 2019). It seems that glucocorticoids should also be potentially effective for ARII, considering the importance of inflammation response in the development and progression of ARII. However, the existing evidence on the use of glucocorticoids in such patients is still inconsistent among studies (Chen et al., 2021; Kochhar et al., 1991). Besides, the current practice guideline and consensus mostly focus on the management of chronic radiation-induced intestinal injury (CRII), rather than ARII (Paquette et al., 2018; Wang and Wang, 2018). Thus, we aim to conduct a multicenter randomized controlled trial (RCT) to explore the efficacy and safety of glucocorticoids for the treatment of ARII.

## 2 Methods

### 2.1 Study design

In this multicenter RCT, patients with grade II-III ARII will be screened. The investigators from each center will sufficiently explain the objectives and harms of this study to potentially eligible participants. Once the participants agree and sign written informed consents, they will be randomly assigned at a ratio of 1:1 to routine treatment alone and in combination with local glucocorticoids groups. The data will be collected at admission, after treatment, and during follow-up periods (Figure 1). This study follows the Declaration of Helsinki, and the ethical approval number from medical ethical committee of the General Hospital of Northern Theater Command is Y (2024) 052-1. It has been registered in the *ClinicalTrials.gov.* Website (registration number: NCT06410443).

**FIGURE 1 F1:**
[figure not shown]
Flowchart of this trial.

### 2.2 Eligibility criteria

The inclusion criteria include: (1) grade II-III ARII; (2) estimated survival time >1 year; (3) age ≥18 years; and (4) signed informed consents.

The exclusion criteria include: (1) absolute contraindications to glucocorticoids; (2) a history of glucocorticoids treatment within 3 months; (3) inflammatory bowel disease or infectious intestinal disease; (4) recurrence of malignant tumor; (5) colorectal cancer or metastasis; (6) severe heart or lung diseases; (7) recent history of surgery or trauma; (8) poorly controlled hyperglycemia and hypertension; (9) active tuberculosis; (10) severe gastrointestinal ulcers; (11) glaucoma; (12) psychiatric diseases; and (13) pregnant or lactating.

### 2.3 Randomization, assignment, and blinding

Participants are stratified according to the grade of ARII at admission, and then randomly assigned to routine treatment alone and in combination with local glucocorticoids groups at a ratio of 1:1 within each stratum. The randomization sequence will be generated by computer system. The trial-group assignments are open-label to the participants and physicians.

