### 2.6 Sample size calculation

Sample size is calculated by using significant difference test in the proportion between two groups on the statistical software PASS 15.0.5 (NCSS, LLC. Kaysville, Utah, United States). The rates of improvement of ARII are estimated as 97.7% and 72.1% in patients treated with and without glucocorticoids according to the results of a previous study by Chen et al. (2021) An alpha value of 0.05, a power of 80%, and a dropout rate of 10% are set. Finally, 30 patients will be required for each group.

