### 2.15 Data analysis

The intention-to-treat (ITT) set comprises all participants randomized. The per-protocol (PP) set consists of participants who complete the assigned treatments of protocol and develop the primary endpoint events without major protocol violation. The safety set contains participants who receive at least one dose of local glucocorticoids and undergo at least one safety evaluation. Continuous variables are described as mean ± standard deviation and median (range) and categorical variables are described as frequencies (percentages). Whitney U test, chi-square test, and Fisher’s exact test are used, if appropriate. A two-sided P value of <0.05 is considered statistically significant. All statistical analyses are performed using IBM SPSS 26.0 software (IBM Corp, Armonk, NY, United States).

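### Allocation is stratified by ARII grade, but every test named in section 2.15 ignores grade; the cost is conservative and its size depends on how prognostic grade is

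*Protocol article*

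**What the plan says.** Section 2.2 admits two grades only, "1) grade II-III ARII", so there are two strata. Under section 2.3, "Participants are stratified according to the grade of ARII at admission", with allocation "at a ratio of 1:1 within each stratum". Section 2.5 makes recovery and improvement the primary endpoints, and both are binary as defined in section 2.7.

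Section 2.15 gives the whole list of comparisons: "Whitney U test, chi-square test, and Fisher’s exact test are used, if appropriate". It adds that "A two-sided P value of <0.05 is considered statistically significant". None of the named tests uses grade.

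Section 2.6 sizes the trial with a "significant difference test in the proportion between two groups", also unstratified. Its inputs are "The rates of improvement of ARII are estimated as 97.7% and 72.1% in patients treated with and without glucocorticoids" and "An alpha value of 0.05, a power of 80%, and a dropout rate of 10% are set", and the result is 30 per group.

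**The concern.** Balancing the arms within grade removes between-grade variation from the treatment contrast. A crude test still counts that variation in its variance. If grade II and grade III patients do differently, the crude test is set against too large a standard error: its true size falls below 5%, and it gives up power that the stratified design has already secured. In a 60-patient trial with two binary primary endpoints, a few points of power matter, and the remedy needs no extra patients or data.

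The point concerns tests that the article does name, not detail that it leaves out.

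**Working it through.** **Planned sample size.** With rates 0.977 and 0.721, two-sided alpha 0.05 and power 80%, the unpooled formula is n = [p1(1−p1) + p2(1−p2)] × (1.960 + 0.842)² / (p1−p2)².

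(0.0225 + 0.2012) × 7.849 / 0.256² = 26.8, so 27 per arm; 27 / 0.9 = 30. The stated figure reproduces and does not depend on a stratified analysis. The checks below use 27 evaluable per arm.

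**Assumptions not in the document.** Grade II and III patients per arm are 14/13 or 18/9. The grade odds ratio (OR) runs from 1 to 10 and is the same in both arms. The overall rate in each arm is held at its stated value. Recovery rates are assumed to be 60% and 30%.

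**Why the crude test becomes conservative.** With no treatment effect and 72.1% improving in both arms, the crude variance uses 0.721 × 0.279 = 0.2012. At OR 5 with 14/13 strata, the grade rates that average 72.1% are 86.6% and 56.4%. The within-grade variance is (14 × 0.866 × 0.134 + 13 × 0.564 × 0.436) / 27 = 0.1786, a ratio of 0.888. The nominal 1.96 then acts as 1.96 / √0.888 = 2.08, which is a two-sided size of about 3.7%. The same steps give 4.4% at OR 3 and 2.8% at OR 10. Exact sizes are slightly higher because counts are discrete.

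**Exact enumeration.** Every possible outcome table was weighted by its binomial probability. With nₘ patients per arm and mₘ responders in stratum m, and T responders on glucocorticoids, CMH without continuity correction is (T − Σmₘ/2)² / Σ[mₘ(2nₘ − mₘ) / (4(2nₘ − 1))], compared with 3.84. The small-count rule means Fisher's test if any expected count is below 5, otherwise chi-square. This is a conventional reading of section 2.15, which does not define the choice.

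True size of the nominal 5% test, 72.1% in both arms:

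| Grade OR | Chi-square | Fisher | CMH |
|---|---|---|---|
| 1 | 5.5% | 2.4% | 4.9% |
| 3 | 4.8% | 2.0% | 4.9% |
| 5 | 4.1–4.2% | 1.6% | 4.7–4.9% |
| 10 | 2.8–3.2% | 1.0–1.2% | 4.6–5.0% |

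The 5.5% at OR 1 is the chi-square approximation at this sample size; grade plays no part there.

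Power for improvement, 97.7% against 72.1%:

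| Grade OR | Chi-square | Small-count rule | CMH | CMH, continuity-corrected |
|---|---|---|---|---|
| 1 | 84.7% | 65.5% | 84.5% | 63.6% |
| 3 | 85.2% | 66.0% | 85.1–85.2% | 65.0–65.1% |
| 5 | 85.7–85.8% | 66.5% | 85.8–86.2% | 66.9–67.1% |
| 10 | 86.4–86.8% | 67.3–67.6% | 86.9–88.1% | 69.9–71.3% |

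Expected failures per arm are 27 × (1 − (0.977 + 0.721)/2) = 27 × 0.151 = 4.1, so the rule picks Fisher's test in about 72% to 74% of trials.

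Power for recovery, assumed 60% against 30% (expected counts are not small, so chi-square applies):

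| Grade OR | Chi-square | CMH | Gain (points) |
|---|---|---|---|
| 1 | 58.6% | 58.7–59.0% | 0 |
| 3 | 58.7–58.8% | 62.7–63.5% | 4–5 |
| 5 | 58.9% | 66.2–67.3% | 7–8 |
| 10 | 59.0–59.1% | 70.4–72.3% | 11–13 |

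The gain depends on the assumed rates. In a simulation at 85% against 50%, with 27 per arm and a grade II share of 50% or 70%, it is under 1 point at OR 3, about 2 at OR 5 and about 4 at OR 10; at OR 1 CMH loses 0.8 to 0.9 point. With 30 evaluable per arm at 60% against 30%, the simulated gains are 1–2, 3–5 and 7–9 points at OR 3, 5 and 10.

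**The case against.** **The analysis plan may add a stratified test.** This is an article, and its list of tests is qualified by appropriateness. That tempers the severity, but does not remove the point: tests are stated for the trial, and none uses the factor by which it randomises. The lack of an effect estimate in section 2.15 is the kind of detail an article may omit, and it is not counted here.

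**Nothing shows that grade matters much.** This stands. A reader might infer from the stratification that grade is the main prognostic factor, but the article gives no outcome by grade and no reason for the choice. At a grade odds ratio of 3 or below, the crude chi-square test is close to nominal.

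**A reader might credit stratification with about 20 points of power for improvement.** The tables do not support this. The gap between the small-count rule and CMH (65.5% against 84.5%) is already there when grade has no effect. It comes from the discreteness of Fisher's test, and a continuity-corrected CMH test loses it again.

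**Fisher's test may be preferred because counts are small.** With the same rate in both arms, set at 84.9% or 90%, the uncorrected CMH test has an exact size of 4.3% to 5.3% over the same grade odds ratios and strata. Small counts at these rates are therefore no strong reason against it.

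**Conclusion.** The mismatch is real: randomisation uses grade, and the stated tests do not. Its direction is conservative. A reader might infer that the crude analysis is invalid or inflates false positives; the figures show the opposite once grade matters. The planned 30 per group also stands on its own inputs.

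The size rests on the assumed grade effect. For improvement at the planned rates, ignoring grade costs a chi-square test about 0 to 1 point. For recovery at an assumed 60% against 30%, it costs about 4 points at a grade odds ratio of 3 and 7 to 13 points at 5 to 10, and less at other rates or with 30 evaluable per arm. This is a modest improvement worth making, because it costs almost nothing.

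**What to change.** In section 2.15, state that the primary test of improvement and of recovery is the Cochran-Mantel-Haenszel test stratified by ARII grade as randomised, without continuity correction. Name the version, because the corrected one gives up most of the power for improvement, and check which one the software prints.

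Report the Mantel-Haenszel risk difference with its 95% CI. It is the average of the within-grade differences, weighted by (n₁ × n₀)/(n₁ + n₀) in each grade, where n₁ and n₀ are the arm sizes; this is a short hand calculation. Keep the unstratified test as a sensitivity analysis, and state in advance whether it is chi-square or Fisher's.

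The cost is analysis wording only, fixed before the data are analysed. Grade at admission is already recorded for randomisation. If grade proves not prognostic, the power lost is under 1 point.

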### 2.4 Treatment

Routine treatment includes antibiotics, probiotics, vitamins, antidiarrheal drugs, enteral nutrition, and endoscopic argon plasma coagulation according to the current practice guideline (Wang and Wang, 2018). These drugs and procedures are selected based on the patients’ disease conditions and their availability at each site.

Local glucocorticoids refer to retention enema of dexamethasone 10 mg combined with 100 mL of 0.9% sodium chloride injection once daily for a duration of 7 days. It requires the solution to be retained in the bowel for more than 1 h.

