### 2.5 Study endpoints

The primary endpoints include the recovery and improvement of ARII after treatment. The secondary endpoints include the recurrence and aggravation of ARII, and adverse events during hospitalization and follow-up periods.

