The grade of intestinal mucosal damage on colonoscopy is evaluated in accordance with the Vienna rectal score (Wachter et al., 2000), as follows.(1) Grade 0 is defined as only localized mucosal hyperemia and edema.(2) Grade 1 is defined as diffuse non-confluent mucosal hyperemia and edema with single telangiectasia but without ulcer, stenosis, and necrosis.(3) Grade 2 is defined as diffuse and confluent mucosal hyperemia and edema with multiple non-confluent telangiectasia but without ulcer, stenosis, and necrosis.(4) Grade 3 is defined as unlimited mucosal hyperemia and edema with multiple and confluent telangiectasia, and the area of superficial ulcer is less than 1 cm^2^, but without stenosis and necrosis.(5) Grade 4 is defined as unlimited mucosal hyperemia, edema, and telangiectasia, and the area of superficial ulcer is more than 1 cm^2^, and the diameter of lumen diameter is more than 2/3 of the regular lumen diameter, but without necrosis.(6) Grade 5 is defined as unlimited mucosal hyperemia, edema, and telangiectasia with deep ulcer, fistula, or perforation, and the diameter of lumen diameter is less than 1/3 of the regular lumen diameter, and presence of necrosis.

Recovery is defined as patients’ clinical symptoms and intestinal mucosal damage on colonoscopy disappear. Improvement is defined as patients’ clinical symptoms alleviate or the Vienna rectal score decreases at least one grade.

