### 2.12 Study schedule

The study treatment and assessment plan are summarized in Table 1.(1) Eligible participants will be enrolled after signing their informed consents.(2) Demographic data, medical history, clinical symptoms, physical examinations, laboratory tests, abdominal computed tomography (CT) images, and description under colonoscopy will be collected before treatment.(3) Repeated abdominal CT scans will be performed on the 6th month after treatment.(4) Repeated colonoscopy will be performed on the 3rd month and 12th month after treatment.(5) Adverse events and survival status will be collected on the 7th day, 1st month, 3rd month, 6th month, and 12th month after treatment.

**TABLE 1 T1:** Study schedule.

Procedure	Screening	Treatment period 7th day	Follow-up period			
			1st month	3rd month	6th month	12th month
Informed consent	√					
Eligibility criteria	√					
Demographic data	√					
Medical history	√					
Clinical symptoms	√	√	√	√	√	√
Physical examinations	√	√	√	√	√	√
Laboratory tests	√	√	√	√	√	√
Abdominal computed tomography	√				√	
Colonoscopy	√			√		√
Adverse events		√	√	√	√	√

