Most of patients with ARII present with mild symptoms and do not require medical care, but 5%–15% of them have to terminate radiotherapy due to severe discomfort, and even develop complications (Hauer-Jensen et al., 2004). In a previous RCT, Chen et al. demonstrated anti-inflammatory effects of glucocorticoids on ARII (Chen et al., 2021). Sixty-eight patients with ARII were randomly assigned to receive either dexamethasone combined with montmorillonite retention enema or oral montmorillonite. Inflammatory cytokines (IL-2 and IFN-γ) levels significantly decreased after treatment, with a more pronounced advantage observed in patients receiving combination dexamethasone (P < 0.001). They also demonstrated more significant response to treatment in terms of clinical improvement (97.67% vs. 72.09%, P < 0.001) and mucosal repairment under colonoscopy (93.02% vs. 65.12%, P < 0.001). Therefore, Chen et al. concluded that patients with ARII could receive more benefits from dexamethasone combined with montmorillonite. However, the evaluation of mucosal repairment, an important criterion for efficacy, was subjective, and lacked detailed descriptions. By contrast, another RCT by Kochhar et al. found a better efficacy of sucralfate than glucocorticoids (Kochhar et al., 1991). Thirty-seven patients were randomly assigned to receive either prednisolone enema combined with oral sulfasalazine or sucralfate enema. Although both two regimens were effective for alleviating clinical symptoms, prednisolone combination treatment was inferior to sucralfate (53.3% vs. 94.1%, P < 0.05). In terms of endoscopic improvement, there was no significant difference between the two groups (46.7% vs. 70.5%, P > 0.05). But two patients withdrew from the trial due to intolerable myalgia and headache in prednisolone enema combined with oral sulfasalazine treatment group. Considering the safety and low cost of sucralfate, Kochhar et al. preferred sucralfate as the better choice for RII (Kochhar et al., 1991). Notably, some of the patients included in the study by Kochhar et al. had CRII with intestinal tissue fibrosis, where anti-inflammatory effects of glucocorticoids might be unsatisfactory.

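### Section 2.3 opens allocation to physicians with no exception for the endoscopist, although the colonoscopic reading enters both primary endpoints and could largely be masked at small cost

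*Protocol article*

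**What the plan says.** Section 2.3, the section that deals with blinding, states: "The trial-group assignments are open-label to the participants and physicians". The article names no masked endoscopist, central reader or blinded assessor.

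Section 2.5 sets the primary endpoints: "The primary endpoints include the recovery and improvement of ARII after treatment". Section 2.7 defines them. For the first, "Recovery is defined as patients’ clinical symptoms and intestinal mucosal damage on colonoscopy disappear". For the second, "Improvement is defined as patients’ clinical symptoms alleviate or the Vienna rectal score decreases at least one grade". On the instrument, "The grade of intestinal mucosal damage on colonoscopy is evaluated in accordance with the Vienna rectal score"; who does the grading is not stated.

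Colonoscopy is done at screening, and section 2.12 adds: "Repeated colonoscopy will be performed on the 3rd month and 12th month after treatment". The enema course in section 2.4 lasts 7 days.

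The Discussion criticises the earlier dexamethasone trial in these terms: "the evaluation of mucosal repairment, an important criterion for efficacy, was subjective, and lacked detailed descriptions".

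**The concern.** The two definitions use the colonoscopic reading differently. Recovery needs both limbs, so no patient can recover unless the reader finds the mucosa clear. Improvement needs either limb, so a fall of one Vienna grade is enough even if symptoms do not change.

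Adjacent lower Vienna grades are separated by calls such as localized or diffuse, confluent or not, single or multiple telangiectasia. A reader who knows the arm and expects the enema to work can shift such calls without intending to, and one grade can change a patient's outcome.

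An enema arm compared with no enema is hard to blind for the patient, so some open-label exposure is unavoidable. The reading of the mucosa is different. It takes place months after a 7-day course, and nothing in the article suggests that the examination itself reveals the arm. If it is read with knowledge of allocation, no limb of either primary endpoint is protected.

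**Working it through.** **The plan's own figure.** Section 2.6 gives 97.7% and 72.1%, alpha 0.05, power 80% and dropout 10%; section 2.15 gives a two-sided test. With the unpooled two-proportion formula:

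n = (1.960 + 0.842)² × (0.977×0.023 + 0.721×0.279) / 0.256² = 26.8, so 27 per arm; 27/0.90 = 30.

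The stated 30 per group reproduces. Nothing here contests it, and masking the reader does not change it. The 27 and 30 serve below as the evaluable and randomized numbers per arm.

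**Illustration of rating bias.** The article gives no misclassification rate, so every input here is an assumption: no true effect; symptom and endoscopic limbs independent; a share u of true endoscopic non-responders read as responders in the enema arm only; uncorrected two-sided chi-square; exact enumeration over both binomials.

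*Improvement (either limb).* With symptom relief s and Vienna improvement v:
- control: 1 − (1−s)(1−v)
- enema arm: the same with v replaced by v + u(1−v)

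For v = 0.50 and u = 0.20, the enema-arm v becomes 0.60.

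| s | Enema v control | Error, n = 27 | Error, n = 30 |
|---|---|---|---|
| 0.50 | 80.0% v 75.0% | 8.03% | 7.27% |
| 0.60 | 84.0% v 80.0% | 7.45% | 6.79% |
| 0.721 | 88.8% v 86.1% | 6.64% | 6.72% |

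*Recovery (both limbs).* With symptom resolution s and mucosal clearance m:
- control: s × m
- enema arm: s × (m + u(1−m))

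For u = 0.20, m = 0.40 becomes 0.52 and m = 0.50 becomes 0.60.

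| s | m | Enema v control | Error, n = 27 | Error, n = 30 |
|---|---|---|---|---|
| 0.50 | 0.40 | 26.0% v 20.0% | 9.02% | 8.31% |
| 0.50 | 0.50 | 30.0% v 25.0% | 7.58% | 7.03% |
| 0.70 | 0.40 | 36.4% v 28.0% | 10.54% | 10.31% |
| 0.70 | 0.50 | 42.0% v 35.0% | 7.90% | 8.35% |

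With u = 0, the same enumeration gives 4.8% to 5.7% across all these rows, so the excess comes from the assumed bias and not from the test.

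With u = 0.30, improvement runs from 8.1% to 11.3% and recovery from 9.6% to 17.1%.

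**The case against.** Several objections have force.

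**The reader is not named.** That the endoscopist knows the allocation is an inference from the word physicians. It is a reasonable one, because the blinding section makes no exception, but the article does not say so outright. A condensed article may leave endoscopy logistics to the full protocol. This tempers the point without removing it, since 2.3 is a positive statement about who is unblinded, not a silence.

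**Masking may not be free.** A reader might infer that it costs no staff time. The article does not support that. It describes no endoscopy staffing, and routine care includes "enteral nutrition, and endoscopic argon plasma coagulation according to the current practice guideline", so an endoscopist may also be a treating physician. Requiring a different physician at every site would need extra staff at some.

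**Colonoscopy may not be the only examiner-rated limb.** Symptom alleviation has no named rater or scale, so a physician may judge that as well.

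**The effect must not be sized on the Vienna grade alone.** At 60% v 50% Vienna improvement, the error rate is 10.2% (n = 27) or 12.3% (n = 30). It is tempting to quote this, but Vienna improvement alone is not a primary endpoint. Under the either-limb definition, an upgraded reading matters only when symptoms did not alleviate, which brings the figure down to 7–8%.

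**The test matters.** Section 2.15 also lists Fisher's exact test, which is conservative here. With a 72.1% rate in both arms, 27 per arm and the upgrading applied directly to that rate, Fisher's error is 2.4% without bias, 3.8% with 20% upgraded and 5.8% with 30%. The bias still acts in the same direction, but the nominal level may not be exceeded.

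**The parallel with the earlier trial is partial.** The Discussion's complaint there is subjectivity and lack of description, not absence of masking. The graded Vienna scale answers the second part. It does not answer the first if the reader knows the arm.

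**Conclusion.** The point stands as a design weakness that is cheap to reduce. Section 2.3 as written leaves the colonoscopic reading, which is judgement-based and feeds both primary endpoints, open to knowledge of allocation. It is not a contradiction in the document, and the open-label design is openly declared.

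Under the assumptions shown, 20% one-directional upgrading takes the type I error to about 7–8% for improvement and about 7–10% for recovery. These are illustrations. They depend on the assumed limb rates, independence of the limbs, the upgrading share and the chi-square test.

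The protection is greatest for recovery, where mucosal clearance is mandatory. For improvement, masking secures only the Vienna route; an open-label judgement of symptoms can still satisfy the endpoint on its own.

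**What to change.** Add to section 2.3:

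- Wherever the endoscopist already doing the month 3 and month 12 colonoscopies is not the treating physician, that endoscopist is not told the allocation and records both the Vienna grade and whether mucosal damage has cleared before seeing the treatment record.
- For every examination, the form records whether the reader was or became aware of the allocation.
- A sensitivity analysis of the primary endpoints is reported, restricted to masked readings.

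The cost is protocol wording, a masked request form and one extra item on the form. No reader, procedure or patient is added, and the sample size stays at 30 per group. Masking will be incomplete at sites where the treating physician also performs endoscopy, and the restricted analysis will have fewer patients, so it should be read as supportive only. The symptom limb of improvement remains open-label, and the report should say so.
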